According to 2020 data, 89% (comprising of 55% adults and 35% children) of those with a HIV positive diagnosis in Nigeria are accessing ART, and out of these, 42% were virally suppressed [1, 10]. Tenofovir disoproxil fumarate (TDF) is one of the most frequently used ART [11]. Currently, more than 80% of PLWHIV in Nigeria were receiving a TDF-based regimen, as Nigeria adopted TDF-based ART as the first-line treatment for HIV in 2014 [1, 12]. Whilst the initial randomised control trials suggest good overall safety for TDF, numerous subsequent studies have shown issues with the renal safety profile, including KTD in various study settings [13]. Furthermore, TDF has also been associated with a wide range of other manifestations of renal impairment than KTD such as low eGFR and rapidly declining eGFR. Globally, the reported incidence of TDF-induced nephrotoxicity ranges between 0.7 and 22% [14, 15]. Likanonsakul et al. [16] in their study reported that approximately 20% of PLWHIV receiving TDF in Thailand had β2-microglobulinuria, a marker of tubular dysfunction. Various risk factors have been associated with KTD including co-morbidities (such as hepatitis C, diabetes mellitus), low body weight, older age, concomitant administration of potentially nephrotoxic drugs, low CD4 count and duration of therapy [17].

In West Africa, a study carried out among a Ghanaian population of PLWHIV taking TDF showed that the prevalence of creatinine clearance less than 60 ml/min/1.73m^2^, dipstick proteinuria and asymptomatic renal tubular dysfunction was 7, 37 and 15% respectively [18]. In Nigeria, little is known about the prevalence of TDF-induced KTD. It is difficult to screen for this complication in resource-poor settings, and very few Nigerian studies have investigated markers of TDF-induced KTD. A study of 57 PLWHIV in Port Harcourt in southern Nigeria suggested an increased burden of KTD in individuals exposed to the TDF regimen. Results showed that after 12 weeks of exposure, 14% of PLWHIV exposed to TDF developed phosphaturia [19].

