This study aims to establish the burden and risk factors for TDF-induced KTD in Nigerians, and explore associations between KTD and polymorphisms in the renal transporter genes as well as *APOL1* risk variants. The study may potentially engender an approach for prevention as well as stemming the burden of CKD in sub-Saharan Africa particularly Nigeria, where GDP per capita is low and budgetary allocation for health is inadequate.

We hypothesise that KTD is common among adult PLWHIV in Nigeria who are receiving TDF-based antiretroviral therapy, and additive contributions from polymorphisms in kidney tubular transporters as well as *APOL1* genetic variants may be associated with the risk of KTD in Nigerians treated with TDF. Further, we hypothesise that the additive contribution from *APOL1* risk alleles would predispose to and enhance the severity of TDF toxicity and that the concomitant use of protease inhibitor may additively influence the susceptibility for severe TDF-induced nephrotoxicity. This paper describes the design and methodology for this study that aims to determine the prevalence and risk factors for TDF-induced KTD in PLWHIV in Nigeria.

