### Setting and study population

The study will be conducted at the Department of Internal Medicine, Ladoke Akintola University of Technology Teaching Hospital (LTH), Osogbo, Nigeria and the Department of Internal Medicine Research Laboratory, University of the Witwatersrand, Johannesburg, South Africa. Participants will be recruited from ART clinics in Nigeria including LTH (Osogbo), Jaleyemi Catholic Hospital (Osogbo), Osun State Hospitals (Asubiaro, Ede, Ikire, Iwo, and Ila Orogun), Adeoyo State Hospital (Oyo State) and Seventh Day Adventist Hospital (Ile-Ife).

For the case-control phase of the study, PLWHIV on a TDF regimen under regular follow up for at least 3 months at the ART clinics who developed proximal KTD will be designated as cases. Research has shown that the median time to nephrotoxicity after TDF initiation is 3.6 months [8], hence, the rationale for a minimum of 3-months on TDF. The controls will be PLWHIV on a TDF regimen under regular follow up for ≥3 months at the ART clinics showing none of the abnormalities suggesting proximal KTD. The cases will be matched one-to-one to controls by gender, age (+/− 5 years), and TDF duration (+/− 3 months) and will be done on an ongoing basis during recruitment of study participants.

Participants meeting the inclusion criteria will be PLWHIV, aged 18 years and above, receiving TDF-containing therapy, on regular follow up for a minimum of 3 months with a viral load of less than 200 copies/ml. The rationale for the use of 3 months cut off point for the duration of tenofovir treatment was based on the results of a previous study by Brennan et al. [8] that showed that the median time to nephrotoxicity after initiation of TDF was approximately 3 months.

The following individuals will be excluded from the study: Individuals with incomplete history of antiretroviral treatment, including HIV treatment status (either treatment-naïve or experienced), date of commencement of ART and combination of ART); persons who are pregnant or lactating; persons with an estimated glomerular filtration rate (eGFR) < 60 ml/min/1.73m^2^ (eGFR will be calculated by Chronic Kidney Disease Epidemiology Collaboration [CKD-EPI] from serum creatinine estimated during the month enrolled in the study); persons with glomerulonephritis, including IgA Nephropathy and Lupus Nephritis; heart failure (NYHA 3 & 4), malignancy and non-Nigerians.

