### Statistical analysis

Descriptive results of continuous variables will be expressed as medians and interquartile ranges. Continuous variables will be tested for normality using the Shapiro–Wilk test and compared using the student’s *t* test or Wilcoxon rank sum test, as required. For the comparison of proportions, the Chi-square test will be used, with Fisher’s corrections applied when needed. Multivariate logistic regression analyses will be performed to identify factors associated with KTD. Parameters with significant *p*-values in the univariate analysis will be entered into a stepwise multivariate analysis. Deviations from Hardy-Weinberg equilibrium of individual alleles and differences in allele frequencies between the two groups will be evaluated by either the chi-square test or Fisher’s exact test where appropriate. Statistical comparisons for genotype frequencies between persons with KTD and those without KTD will be made by the chi-square test or Fisher’s exact test. Associations between allele sets or haplotypes and the risk of TDF-induced KTD will be estimated by computing odds ratios and 95% confidence intervals from multivariable logistic regressions. This analysis will include adjustments for demographic characteristics (age, sex, and BMI), baseline eGFR, duration of HIV infection, protease inhibitor therapy, and other antiretroviral treatment. All statistical analyses will be conducted using Stata 12 and R statistical software. *P* values < 0.05 will be considered statistically significant. Methods for controlling the false discovery rate and Bayesian analysis under shrinkage priors will be used when reporting the results of multivariable logistic regression.

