## Discussion

Individuals of African descent have an increased risk of developing CKD, with CKD in non-HIV individuals 3–4 times more common in Africa than in developed countries [5, 6]. In Nigeria, 38–53% of PLWHIV develop CKD [35, 36]. The high prevalence of kidney disease in sub-Saharan Africa coupled with the initiation of TDF-based regimens in PLWHIV at risk of kidney failure highlights the need to regularly screen PLWHIV for renal dysfunction, including KTD to reduce the burden of nephrotoxicity.

There has been increasing interest in the pharmacogenomics of renal drug transporters as a useful tool for identifying individuals who might be at risk of developing KTD, as it allows for a personalised approach to the use of TDF in PLWHIV on antiretroviral therapy. However, it is difficult to screen for genetic markers of KTD in resource poor areas, and to date no African study has investigated genetic markers of KTD. Moreover, previous studies on the pharmacogenetics of KTD in PLWHIV who were treated with TDF have provided diverse results [32, 33, 37]. Several factors could induce KTD, including infection, inflammation, pre-existing kidney disease, concurrent use of nephrotoxic drugs and diabetic kidney disease, and it is therefore difficult to evaluate whether KTD is exclusively caused by TDF. Thus, the role of genetic polymorphisms in drug transporter genes on TDF-induced KTD remains to be distinguished and isolated from other aforementioned risk factors for KTD, especially in individuals of African descents.

Based on this background, this study was designed to identify those risk factors that may be associated with TDF-induced KTD in Nigerian PLWHIV who are receiving a TDF regimen with suppressed viral load, and free of pre-existing kidney impairment and major comorbidities. This study also seeks to investigate the interaction between these risk factors and genetic predisposition as well as the interaction between polymorphisms in drug transporter genes and *APOL1* genetic variants.

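### Baseline eGFR in the multivariable genetic models is measured on TDF, so adjusting for it, and excluding values below 60, can pull the genetic odds ratios down, above all for APOL1

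*Protocol article*

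**What the plan says.** All references are to the protocol article.

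- **Exposure before entry** (Setting and study population): participants are "receiving TDF-containing therapy, on regular follow up for a minimum of 3 months", and the rationale given makes 3 months the minimum time on TDF.
- **Exclusion** (same section): "persons with an estimated glomerular filtration rate (eGFR) < 60 ml/min/1.73m^2" are excluded, with eGFR calculated "from serum creatinine estimated during the month enrolled in the study".
- **Meaning of baseline** (Recruitment of participants): serum creatinine and eGFR are listed as baseline laboratory data on the case report form completed after consent. No pre-TDF value is described, and Strengths and limitations says that no longitudinal data will be collected.
- **Adjustment** (Statistical analysis): odds ratios for allele sets or haplotypes come from multivariable logistic regression adjusted for age, sex, BMI, "baseline eGFR, duration of HIV infection, protease inhibitor therapy, and other antiretroviral treatment".
- **Outcome** (Diagnostic criteria for KTD): plasma creatinine enters both the phosphorus resorption and the uric acid excretion criteria.
- **Premises** (Background): "TDF has also been associated with a wide range of other manifestations of renal impairment than KTD such as low eGFR and rapidly declining eGFR"; APOL1 accounts for almost 70% of the excess kidney disease risk in people of African descent; and APOL1 risk alleles "would predispose to and enhance the severity of TDF toxicity".
- **Intended population** (Discussion): "free of pre-existing kidney impairment and major comorbidities".

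**The concern.** A confounder of a gene-outcome association must be associated with genotype without being its result. Enrolment eGFR cannot cause a germline variant. By the Background's own account, it can be lowered by TDF injury and by APOL1. It also shares plasma creatinine with two KTD criteria. Adjusting for it, or selecting on it, therefore conditions on a possible consequence of both genotype and outcome. Where the risk allele and KTD both lower eGFR, the odds ratio moves downward: a real effect shrinks, and a null variant can look protective. The association of the candidate SNPs with KTD is a primary outcome.

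The exclusion has a second consequence. An eGFR taken on treatment cannot separate impairment that preceded TDF from loss on TDF. The sample is therefore not selected as "free of pre-existing kidney impairment and major comorbidities": people whose eGFR fell below 60 on TDF are removed too, although the Background hypothesises about severity of toxicity.

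**Working it through.** **1. The plan's own figure.** Inputs from Sample size and power analysis: MAF 0.19, dominant model, KTD prevalence 13%, alpha 0.003 (0.05/18), power 80%, OR 1.75. Carrier frequency is 1 - 0.81² = 0.344. Solving for carrier frequency in cases and controls gives 0.459 and 0.327. The two-sided two-proportion formula gives 393 per group at alpha 0.003 and 398 at 0.05/18, against 398 in Table 1. Power at 400 per group is 0.81. The sample size is not in dispute.

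**2. Effect of adjustment.** The document gives no effect of genotype or KTD on eGFR, so these are assumptions. Let eGFR be normal with SD σ within each genotype-by-KTD group, lowered by a in carriers and by b in KTD. Bayes' rule then gives

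log OR(adjusted) = log OR(true) - ab/σ², so OR(adjusted) = OR(true) × exp(-ab/σ²).

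In this model, truncating at 60 adds nothing further once eGFR is a covariate. With σ = 20, σ² = 400:

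| a, b (ml/min) | Factor | True OR 1.75 becomes | True OR 1.00 becomes |
|---|---|---|---|
| 0, 10 | exp(0) = 1.00 | 1.75 | 1.00 |
| 2, 5 | exp(-10/400) = 0.975 | 1.71 | 0.98 |
| 5, 10 | exp(-50/400) = 0.88 | 1.54 | 0.88 |
| 10, 10 | exp(-100/400) = 0.78 | 1.36 | 0.78 |

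With σ = 18 (σ² = 324), the last two rows for a true OR of 1.75 become 1.50 and 1.29. Simulation of 1,000,000 people per scenario at that SD, with restriction and adjustment, gave 1.51 and 1.29.

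**3. Effect of exclusion alone.** With S(g,k) the probability of eGFR of at least 60 in genotype g and KTD status k,

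OR(restricted) = OR(true) × S(1,1)S(0,0) / [S(1,0)S(0,1)].

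Assume a mean of 95 in non-carriers without KTD, and SD 20:

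- a = 5, b = 10: 1.75 × (0.841 × 0.960)/(0.933 × 0.894) = 1.69.
- a = 10, b = 10: 1.75 × (0.773 × 0.960)/(0.894 × 0.894) = 1.62.
- a = 0, b = 10: the terms cancel, giving 1.75.

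**4. The severity hypothesis.** Suppose KTD lowers eGFR by 10, by a further 15 in carriers with KTD, and genotype has no other effect. Exclusion alone gives 1.75 × 0.692/0.894 = 1.35 (SD 20). Simulation at SD 18 gave 1.36 by exclusion alone, 1.50 by adjustment alone and 1.28 with both. The exclusion then removed 29% of carrier cases and 8% of non-carrier cases.

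**5. What this does to power.** Treating the shifted odds ratio as the effect to be detected, with 400 per group and alpha 0.003 as in step 1:

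- OR 1.54: carrier frequencies 0.432 and 0.331, power about 0.49.
- OR 1.36: carrier frequencies 0.406 and 0.335, power about 0.19.

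These are approximate, because they use the unadjusted two-proportion formula.

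**The case against.** **The bias is conditional.** This stands. If KTD lowers eGFR equally in everyone and genotype has no other route to eGFR, nothing is biased (first row of the table), and small effects give a small shift. A reader might infer that all 18 SNP odds ratios are pulled down. The document supports a route from gene to kidney function for APOL1, which has 3 of the 18 SNPs. For the 15 transporter SNPs it states no direct effect on eGFR, so there the concern depends on carriers with KTD losing more eGFR.

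**Adjustment may control for prior kidney disease.** An unmeasured cause of both low eGFR and KTD does not confound a genotype that is independent of it. In simulation (SD 18), such a cause left the OR at 1.70 unadjusted and 1.71 adjusted, so adjustment buys almost nothing.

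**Part of the plan escapes.** The chi-square and Fisher comparisons of genotypes and alleles do not use eGFR, so they avoid the adjustment but not the exclusion. The separate risk-factor model does not name eGFR, so the point does not extend to it.

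**Stronger readings that the document does not support.**

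- That the exclusion removes the severe cases. It removes toxicity severe enough to bring eGFR below 60. Marked tubular dysfunction with eGFR of at least 60 stays in, and urinary RBP and NAG are still studied.
- That prevalence is understated by a known amount. The document gives no KTD rate among those excluded. Only the change of target population is certain.
- That eGFR and KTD are measured at one visit. The text fixes only the enrolment month.
- That the eGFR issue invalidates the term TDF-induced. Attribution is a separate matter, and the Discussion already concedes that "it is therefore difficult to evaluate whether KTD is exclusively caused by TDF".

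**Conclusion.** The concern holds in conditional form. The text fixes an on-treatment eGFR as both an exclusion and a covariate in the multivariable genetic models, and the Background itself places eGFR downstream of TDF injury and APOL1. For APOL1, the covariate cannot be defended as confounder control.

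The tabulated range, from no bias to 1.36 for a true OR of 1.75, rests on assumed shifts in eGFR and an SD of 20. The document supplies none of these, so the range shows what is possible and is not a forecast. OR 1.75 is the effect for which the study was sized, so the larger shifts would matter for a primary outcome. The description of the sample as having no kidney impairment before TDF is unsupported whatever those values are.

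**What to change.** 1. Leave enrolment eGFR out of the primary allele-set and haplotype model. Show it only in a sensitivity model labelled as conditioning on an on-treatment measurement.
2. Where clinic records hold a pre-TDF creatinine, use that as baseline eGFR.
3. State the prevalence and severity conclusions for virally suppressed TDF users with eGFR of at least 60. The severity hypothesis can stay within that limit.
4. In the Discussion, replace the kidney part of "free of pre-existing kidney impairment and major comorbidities" with a statement that eGFR was at least 60 at enrolment.

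The cost is a narrower stated target population, one extra sensitivity model and a search of clinic records for pre-TDF values. With 2491 participants enrolled by June 2020, the exclusion is largely fixed, but the model and wording can still change. The sample size need not change.

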### Sample size and power analysis

At least 3000 participants will be recruited for the cross-sectional study from which 400 cases and 400 matched controls will be selected for the case-control sub-study. The sample size was calculated based on the following assumptions. Utilising 1000 Genomes data, we estimated the minor allele frequency (MAF) within the population, using the Yoruba in Ibadan (Nigeria) as a proxy for our study population [26]. The rare polymorphism, rs9349256 has the lowest MAF of 0.01 while the common polymorphism, rs717620 has the highest MAF of 0.42, the average MAF being 0.19. In addition, a Bonferroni correction was incorporated by setting our alpha level at 0.003 (0.05/18) to account for the multiple comparison testing. With the aid of a web browser program for basic sample size calculations of single nucleotide polymorphism (SNP) studies [27–29] [http://biostats.usc.edu/Quanto.html] and using a dominant inheritance model, the average MAF of 0.19, 13% KTD prevalence [30], a power of 80% and an alpha of 0.003, a sample size of 400 cases and 400 controls is able to detect a minimum odd ratio (OR) of 1.75 (case control phase). Table 1 indicates the required sample size (per group using a dominant model) to detect different odds ratios. Based on the data from a previous study in Nigerian PLWHIV which reported the prevalence of TDF-induced KTD as 13%, we made an assumption that 13% of TDF-treated individuals will develop KTD [30]. Therefore, taking this into consideration, the number needed to be screened to identify 400 cases is approximately 3000. We will therefore screen 3000 participants in the cross-sectional phase of this study.

**Table 1 Tab1:** Calculations of the sample size (per group using a dominant model), required to detect different odds ratios in case-control analysis, assuming alpha = 0.003; power = 80% and ratio cases/controls = 1

Odds ratio	Sample Size (N)
1.25	2531
1.50	760
1.75	398
2.00	260
2.25	191
2.50	150
2.75	124
3.00	106

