### Laboratory procedures

Blood and urine samples will be collected for routine laboratory measurements and the measurement of markers of renal function and proximal tubulopathy. The latter tests will be performed by LTH clinical laboratory services using an ADVIA® 1800 Chemistry System (Siemens, Germany). Blood samples will be used for creatinine, urea, electrolyte, uric acid and glucose measurements. Serum creatinine will be measured using the Jaffe method. A 24-h urine sample will be collected to measure protein, glucose, phosphate, uric acid and creatinine. Participants will be fasted overnight for at least 8 h and allowed to drink ad libitum. Spot urine samples will be collected and stored at − 80 °C for urinary RBP and NAG analysis using the RBP Urinary Competitive ELISA kit (ThermoFisher Scientific) and NAG ELISA Kit (R&D Systems, Inc. Minneapolis, USA).

An additional blood sample will be drawn for genomic DNA extraction. Samples will be collected into ethylenediaminetetraacetic acid (EDTA) vacutainers and stored at − 20 °C until DNA extraction. Genomic DNA will be extracted from the whole blood and the concentrations determined using a Qubit fluorometer (Thermo Fisher Scientific). DNA will be aliquoted and stored at − 80 °C.

The 18 SNPs to be genotyped are outlined in Table 2. Candidate SNPs were selected based on previously reported functional significance and minor allele frequencies > 5% in the literature [16, 32, 33]. SNPs will be genotyped using the rhAmp SNP Genotyping Assays. The rhAmp SNP assays provide a highly accurate, PCR-based genotyping method. The method is based on RNase H2-dependent PCR (rhPCR) and has improved specificity over TaqMan and KASP technologies [34]. The SNP genotyping will be carried out at the Internal Medicine Research Laboratory, University of Witwatersrand, South Africa.

**Table 2 Tab2:** List of selected Single Nucleotide Polymorphisms

SNP	Gene	Chromosome	Position	Alleles
rs717620	ABCC2	Chromosome 10	99782821	C > T
rs2273697	ABCC2	Chromosome 10	99804058	G > A
rs17222723	ABCC2	Chromosome 10	99836239	T > A
rs3740066	ABCC2	Chromosome 10	99844450	C > T
rs8187710	ABCC2	Chromosome 10	99851537	G > A
rs899494	ABCC4	Chromosome 13	95209550	G > A
rs1751034	ABCC4	Chromosome 13	95062722	T > C
rs3742106	ABCC4	Chromosome 13	95021537	A > C
rs9349256	ABCC10	Chromosome 6	43404511	G > A
rs2125739	ABCC10	Chromosome 6	43445127	T > C
rs1045642	ABCB1	Chromosome 7	87509329	C > T
rs1128503	ABCB1	Chromosome 7	87550285	C > T

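### The single-SNP tests are sized at a Bonferroni alpha of 0.003 but, as the analysis section is written, would be judged at an unadjusted 0.05

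*Protocol article*

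**What the plan says.** The opening of Methods/design lists the association of candidate SNPs with KTD among the primary outcomes, alongside KTD prevalence. Under Laboratory procedures, "The 18 SNPs to be genotyped are outlined in Table 2".

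Sample size and power analysis states that "a Bonferroni correction was incorporated by setting our alpha level at 0.003 (0.05/18) to account for the multiple comparison testing". It sets out its inputs as "the average MAF of 0.19, 13% KTD prevalence [30], a power of 80% and an alpha of 0.003", under a dominant inheritance model, and concludes that "a sample size of 400 cases and 400 controls is able to detect a minimum odd ratio (OR) of 1.75". Table 1 and the power simulations for the rarest and commonest variants also use 0.003.

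The Statistical analysis section mentions neither 0.003 nor Bonferroni. It assigns the comparisons of allele and genotype frequencies to chi-square or Fisher's exact tests, and the odds ratios for allele sets or haplotypes to multivariable logistic regression. P values below "0.05 will be considered statistically significant", with no limit to particular analyses. The next sentence reads: "Methods for controlling the false discovery rate and Bayesian analysis under shrinkage priors will be used when reporting the results of multivariable logistic regression".

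**The concern.** For one primary question the article gives a sizing alpha, a general significance threshold and a partial multiplicity provision, and does not say which of them decides a SNP finding. A SNP with p = 0.04 in the genotype test is significant under the Statistical analysis section and not significant at the alpha on which the study was sized. The false discovery rate sentence does not settle this, because the single-SNP chi-square and Fisher tests are not multivariable logistic regression.

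Two things are at stake. One is false positives in a candidate-gene study whose Discussion says earlier pharmacogenetic results were mixed and presents such markers as a route to personalised use of TDF. The other is that the stated power describes a different test from the one that, read literally, makes the decision.

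**Working it through.** **Inputs.** From Sample size and power analysis: MAF 0.19, dominant model, KTD prevalence 13%, OR 1.75, alpha 0.003, power 80%, and in Table 1 "power = 80% and ratio cases/controls = 1". From Setting and study population: "The cases will be matched one-to-one to controls by gender, age (+/− 5 years), and TDF duration (+/− 3 months"). From Table 2: 18 SNPs in seven genes (ABCC2 5, ABCC4 3, ABCC10 2, ABCB1 2, SLC22A6 2, SLC22A11 1, APOL1 3). Sidedness is not stated; I take two-sided, and step 1 bears this out.

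**1. Reproduce the plan's sample size.**
- Carrier frequency: 1 − (1 − 0.19)² = 0.344.
- Carrier proportions at OR 1.75 and 13% prevalence: p₁ = 0.459 in cases, p₀ = 0.327 in controls.
- Matched pairs: probability of a discordant pair d = p₁(1 − p₀) + p₀(1 − p₁) = 0.486. Share of discordant pairs in which the case is the carrier: θ = 1.75/2.75 = 0.636.
- Likelihood-ratio information per pair: λ = 2d[θ ln θ + (1 − θ) ln(1 − θ) + ln 2] = 0.0366.
- n = (z for alpha/2 + z for power)²/λ = (2.968 + 0.842)²/0.0366 = 396.5, so 397 per group against 398 in Table 1.

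The same formula gives 2530, 759, 397, 259, 190, 150, 124 and 106 for the eight rows, against 2531, 760, 398, 260, 191, 150, 124 and 106 in the table. For OR 1.75 an unmatched formula gives 393, and one-sided versions give 349 to 353. The table was therefore computed at two-sided 0.003.

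**2. Sample size and power by threshold (OR 1.75).** Matched formula; power = Φ(√(400λ) − z for alpha/2).

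| Alpha | n per group for 80% power | Power at 400/400 |
|---|---|---|
| 0.003 | 397 | 80.5% |
| 0.05/18 = 0.00278 | 402 | 79.8% |
| 0.05 | about 214 | 97% |

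The unmatched calculation gives 81% at 0.003 and 97% at 0.05.

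**3. Chance of at least one false SNP finding, all nulls true, one test per SNP.**
- Independent tests at 0.05: 1 − 0.95¹⁸ = 60.3%, with 18 × 0.05 = 0.9 false positives expected.
- Independent tests at 0.003: 1 − 0.997¹⁸ = 5.3% (Bonferroni bound 18 × 0.003 = 5.4%).
- Independent tests at exactly 0.05/18: 4.9%.

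**4. Sensitivity to correlation.** SNPs in the same gene may be correlated, and the article gives no linkage figures. I simulated 18 null test statistics in the seven gene blocks (200,000 runs), with the within-gene correlation as an assumption.

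| Assumed within-gene correlation | At 0.05 | At 0.003 |
|---|---|---|
| 0 | 60% | 5.2% |
| 0.3 | 58% | 5.2% |
| 0.5 | 55% | 5.0% |
| 0.7 | 50% | 4.5% |
| 0.9 | 42% | 3.5% |
| 0.99 | 34% | 2.5% |

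Testing both alleles and genotypes adds tests that these figures do not count.

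**5. If a false discovery rate method did cover the 18 tests.** With Benjamini-Hochberg at an assumed 5%, the chance of any false finding with all nulls true is about 4% to 5% over the same correlations. The 34% to 60% therefore describes only tests left at an unadjusted 0.05.

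**The case against.** The strongest reply is that the plan does not ignore multiplicity. The sentence straight after the 0.05 threshold brings in false discovery rate control and shrinkage priors, and does so for the regression that yields the adjusted genetic odds ratios. Since 0.003 is itself 0.05/18, the 0.05 could also be read as the overall level to which a correction is then applied. The false discovery rate level and the family of tests are details that an article commonly leaves to the full plan.

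Much of this stands. A reader might infer that the study as a whole carries a 60% chance of a false SNP finding, or that the authors have committed to calling all their genetic results at an unadjusted 0.05. The documents do not support either reading. The regression has a multiplicity provision, and 60% is the upper end for one test per SNP, reached only with independent, unadjusted tests and every null true. I also make nothing of the missing false discovery rate level, or of rounding 0.00278 to 0.003, which moves the bound only from 5.0% to 5.4%. A looser threshold raises power, so the adequacy of 400/400 is not in doubt.

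What the reply does not reach is the set of single-SNP chi-square and Fisher tests. The article assigns allele and genotype comparisons to them, the false discovery rate sentence does not extend to them, and the only threshold stated for them in the analysis section differs from the design alpha. That is a conflict between two stated rules rather than a detail left out.

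**Conclusion.** The point holds in this limited form and should be fixed. The sizing alpha of 0.003, the general 0.05 threshold and the regression-only false discovery rate provision are not reconciled for a primary outcome, and the single-SNP tests have no multiplicity control as written. If those tests are judged at 0.05, the chance of at least one false finding is about 34% to 60%, against about 5% or less at the design alpha. The range assumes all nulls true, one test per SNP, and within-gene correlations between 0 and 0.99 that I chose because the article gives none. The stated 80% power is right for the 0.003 test (80% to 81% at 400/400) and does not describe a 0.05 test (97%).

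**What to change.** In Statistical analysis, state that each of the 18 single-SNP tests in the case-control set is judged at the design alpha of 0.003 in one named primary model (the sizing used the dominant model). Confine P < 0.05 to the non-genetic risk-factor analyses. Keep the planned false discovery rate and shrinkage methods for the multivariable regression, and say how their results relate to the primary SNP call.

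The cost is two or three sentences, written before genotype results are seen. Keeping 0.003 leaves 400/400 unchanged. If exactly 0.05/18 (0.0028) is preferred, the matched formula needs about 402 per group, or 79.8% power at 400, a negligible difference.
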